### Diagnostic criteria

2.3

The included participants will meet the following Western Medicine and TCM diagnostic criteria.

#### Western medicine diagnostic criteria

2.3.1

Regarding the diagnostic criteria for cerebral infarction/cerebral hemorrhage, a confirmed diagnosis will be obtained through brain computed tomography (CT) or MRI, with reference to the Chinese guidelines for diagnosis and treatment of acute ischemic stroke and cerebral hemorrhage, at the Cerebrovascular Disease Section in Chinese Neurology Branch of Medical Association in 2014. The diagnosis for dysphagia will refer to the diagnostic criteria for post-stroke dysphagia rectified during the sixth National Academic Conference on Cerebrovascular Disease.

#### TCM diagnostic criteria

2.3.2

Regarding the diagnostic criteria for cerebral infarction/cerebral hemorrhage, a confirmed diagnosis will be obtained through brain CT or MRI, with reference to the management guidelines for common diseases in internal medicine of TCM (ZYYXH/T19-2008). Dysphagia diagnosis will refer to the diagnostic criteria for post-stroke dysphagia rectified during the sixth National Academic Conference on Cerebrovascular Disease.

### Inclusive criteria

2.4

The inclusion criteria will be as follows: clinical diagnosis of first-episode unilateral cerebral hemisphere infarction or cerebral hemorrhage, with confirmation using CT or MRI; meeting the diagnostic criteria for dysphagia; showing abnormal expressions of the oral and pharynx stages upon VFSS evaluation; having stroke and dysphagia duration within 3 months; being conscious with stable vital signs and a mini-mental state examination score of ≥ 21; age 45 to 75 years; and having provided informed consent.

### Exclusion criteria

2.5

The exclusion criteria will be as follows: having a non-unilateral lesion; having a history of stroke, cerebral tumor, brain impairment, and other neuropsychiatric problems; having a history of dysphagia; having other cognitive disorders, aphasia, or serious cardiopulmonary and renal complications; and being unable to cooperate with examination and treatment.

### The drop out of cases and disposal

2.6

The criteria for drop-out cases will be as follows: voluntary withdrawal from the study; being unsuitable for further assessment due to severe adverse reactions, severe complications, or condition deterioration; poor compliance that impedes the provision of consent for study participation; or incomplete treatment evaluation without rule compliance and with insufficient observation data.

Regarding the disposal of drop-out cases, researchers should adopt home visits, phone, letters, etc to communicate with the participants, record the last treatment time, and extensively perform evaluation. After obtaining the drop-out reasons, they will be added to the case report form. All observation data from drop-out cases will be collected for analysis by the project teams. The researcher should record details regarding drop-out information and enroll more than one treatment course to be included in the efficient statistics.

### The discontinuity and management of cases

2.7

Participants shall be discontinued during the trials in case of occurrence of serious adverse reactions, severe complications, or condition deterioration. Moreover, the clinical trials will be suspended according to the doctors’ judgment, if required.

Regarding management of discontinued cases, the doctor will take some relevant clinical disposals after discontinuation. Subsequently, the doctor will perform a detailed investigation of the reasons and retain the obtained observation data. The last obtained result will be used as the final result and included in the analysis of efficacy and adverse reactions.

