## Introduction

1

Stroke, which is also known as cerebral apoplexy, is characterized by high morbidity, mortality, recurrence, and disability rates; moreover, it has the second-highest mortality rate worldwide.^[1,2]^ The increasing stroke incidence in the young population is a significant public health issue. Moreover, the stroke burden has been increased by general population growth and the increasingly aging population.^[3]^

Stroke can cause several sequelae, including motor dysfunction, sensory dysfunction, cognitive function, and swallowing dysfunction. Approximately 65% of patients with acute stroke present dysphagia.^[4]^ Post-stroke damage to the brain, cerebellum, or brain stem can impair swallowing function.^[5]^ Swallowing difficulties cause several problems, including aspiration and malnutrition, which can cause further complications. Among them, pneumonia is the main mortality cause in patients with stroke; moreover, there is a need to address socioeconomic issues, such as long-term medical expenses.^[6,7]^

There has been rapid development and progress in modern rehabilitation technology, swallowing training, transcranial magnetic stimulation, electrical stimulation, and other methods, which allow significant improvements in post-stroke swallowing disorders. Acupuncture is an important treatment method in traditional Chinese medicine for rehabilitation. It has a definite effect, simple and easy operation, and less toxicity and side effects. It is a common clinical method for stroke treatment, including scalp acupuncture, nape acupuncture, tongue acupuncture, body acupuncture, and other needle methods. Currently, there have been numerous acupuncture studies on stroke treatment, including post-stroke swallowing dysfunction. Numerous clinical reports have indicated that acupuncture can significantly improve swallowing function.^[8,9]^ However, there remains no high-quality and effective evidence clearly showing acupuncture-mediated recovery of stroke and swallowing disorders.^[10]^

Consequently, the proposed study will use commonly used rating scales, surface electromyography (sEMG) signals, and functional magnetic resonance imaging (fMRI) to examine the acupuncture efficacy in the treatment of swallowing dysfunction in patients with stroke.

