**Figure 1 F1:**
[figure not shown]
Present the technology roadmap.

**Table 1 T1:** Clinical observation flow charts.

Research stage	Selection period	Treatment period		Follow-up period
Evaluation times	First time	Second	Third time	Fourth
Evaluation time point	1 and 0 days before treatment	1 week after intervention	2 weeks after intervention	1 month after the end of the intervention
Inclusion criteria	•			
Exclusion criteria	•			
Informed consent form	•			
Online random grouping	•			
General assessment				
General information	•			
Current medical history/allergic history	•			
Past history/complications	•			
Evaluation of the curative effect index				
VFSS	•		•	
SSA	•	•	•	•
Surface electromyography signal	•	•	•	
Improved Barthel index	•	•	•	
SS-QOL				•
Security assessment				
Life indication	•	•	•	•
Other assessments				
Adverse reactions/events		•	•	
Recurrence situation				•
Treatment compliance			•	

SSA = standardized swallowing assessment, SS-QOL = stroke-specific quality of life scale, VFSS = videofluoroscopic swallowing examination.

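### Section 2.7 applies a last-result rule to adverse reactions in patients stopped for harm; read literally, it may leave later events, worsening or death out of the safety analysis, and it needs reconciling with Section 2.6

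*Protocol article*

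**What the plan says.** Section 2.7 first says who is stopped: "Participants shall be discontinued during the trials in case of occurrence of serious adverse reactions, severe complications, or condition deterioration". After the stop there is clinical care, and "the doctor will perform a detailed investigation of the reasons and retain the obtained observation data". The analysis rule follows: "The last obtained result will be used as the final result and included in the analysis of efficacy and adverse reactions".

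Section 2.6 uses the same reasons to define one kind of drop-out: "being unsuitable for further assessment due to severe adverse reactions, severe complications, or condition deterioration". For drop-outs it says that "researchers should adopt home visits, phone, letters, etc to communicate with the participants, record the last treatment time, and extensively perform evaluation", and that "All observation data from drop-out cases will be collected for analysis by the project teams".

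In Table 1 the row "Adverse reactions/events" is marked at weeks 1 and 2 only. The 1-month follow-up column is marked for vital signs and recurrence, but not for adverse events.

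Section 2.17 carries missing values forward for key indicators in the full analysis set. It does not mention adverse events.

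**The concern.** A last-result rule suits a quantity measured repeatedly on a scale, where the latest value stands in for a missing later one. Adverse events are a running record. What matters is whether, how often and how severely they occurred over a period, and the latest entry does not summarise that.

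The rule also falls on patients selected for having come to harm, in whom further harm is most plausible. The Introduction says that "pneumonia is the main mortality cause in patients with stroke", and names aspiration among the consequences of dysphagia. A patient stopped for deterioration could develop such a complication afterwards. If the last result before the stop is final for safety, that outcome could be missing from the comparison. If the arms also differed in how many patients are stopped, the omission would be unequal between them.

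**Working it through.** The document gives no adverse-event rate, number of discontinuations or time to discontinuation, so there is no figure to reproduce. The check sets the passages side by side.

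1. **Scope of the rule.** One sentence in Section 2.7 names efficacy and adverse reactions together. The last-result rule therefore covers safety by its own wording.

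2. **Which result is the last.** The sentence before it speaks of retaining data already obtained. Section 2.7 provides for care and for finding out why the patient stopped, but names no further event recording. Section 2.6 describes patients with the same reasons as not suitable for further assessment. Together these make the stop a natural cut-off, although neither section defines it as one.

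3. **What points the other way.** Section 2.6 asks for contact, evaluation and collection of all observation data. It names no adverse-event follow-up and no period; the specific items it lists are the last treatment time and the drop-out reason. Even if later events were collected, Section 2.7 would still make the last result final for analysis.

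4. **Which safety measures would be affected under the literal reading.**

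| Patient | At least one event (yes/no) | Number of events, worst severity, death |
|---|---|---|
| Stopped for an adverse reaction | Already yes at the stop; unchanged | May be understated |
| Stopped for deterioration or a complication recorded as an adverse event | Already yes at the stop; unchanged | May be understated |
| Stopped for deterioration or a complication not recorded as an adverse reaction, with no earlier event | May stay no although an event follows | May be understated |

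5. **Size.** For the yes/no measure, the share of an arm that is missed equals b × q. Here b is the share of the arm in the third row, and q is the chance of a first event between the stop and the end of the safety period. The document gives neither. The 30% loss in Section 2.16 cannot stand in for b, because it is an allowance for all drop-out and elimination, and Sections 2.6 and 2.8 include voluntary withdrawal, poor compliance and protocol violations among the reasons.

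6. **Window.** Scheduled adverse-event assessment ends at week 2 for every patient. On the present schedule, the rule can remove at most about two weeks of scheduled assessment. The absence of a 1-month entry applies to completers too and is not caused by Section 2.7.

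**The case against.** The strongest case against is that the sentence is an inclusion rule: discontinued patients stay in both the efficacy and the safety analysis. Section 2.7 does not say that recording ends at the stop, and it does not define the last result as one obtained before it. Section 2.6 asks for contact, evaluation and all data in patients with the same reasons. Section 2.17 does not extend carrying forward to adverse events, and a third party will write the detailed analysis plan.

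Much of this stands. A reader might infer that the safety record closes at the stop and that later harm is not counted. The text permits that reading but does not state it, and Section 2.6 speaks against it. A reader might also want to estimate a share of events lost, or a shrunken difference between arms. Neither follows, because a patient stopped for an adverse reaction is already counted as having an event. It would also be too strong to say that a patient stopped in the first week has no safety information: no scheduled entry exists yet, but Section 2.7 has the reason for the stop investigated.

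The objection does not remove the point. Leaving detail to an analysis plan explains silence, but here the protocol states a rule, and the rule does not suit event data. Section 2.6 does not say that events after the stop enter the safety analysis. Staff and the statistician would have to choose between the two sections.

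**Conclusion.** The point holds as a defect of wording and method. Section 2.7 applies a last-value rule to cumulative event data, in patients stopped for harm, and it does not fit well with Section 2.6. Under the literal reading, later distinct events, worsening and deaths may be left out. So may first events in patients stopped for deterioration or complications that were not recorded as adverse reactions. Under the inclusion reading, little or nothing is lost.

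No size can be given. The effect depends on how many patients are stopped without a recorded event, how often events follow, and which reading the sites and the statistician adopt. None of these is in the document. The present schedule limits the scheduled window at risk to about two weeks. The change is still worth making because it is cheap and it concerns the patients in whom later harm is most plausible.

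**What to change.** - **Section 2.7:** limit the last-result sentence to efficacy.
- **Safety recording:** state that for every treated patient, including those discontinued, all adverse events are recorded to the end of one common, defined period. The existing 1-month contact could serve as its end, with the contact routes in Section 2.6 for patients who cannot attend. If that contact is chosen, Table 1 needs an adverse-event entry there for all patients.
- **Safety reporting:** report by randomised group the number of patients with at least one event, plus serious events and deaths, with no carrying forward.
- **Section 2.6:** reconcile it with Section 2.7, so that being unsuitable for further assessment does not end safety recording.

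The cost is a few wording changes and modest extra adverse-event recording at a contact that already exists. This covers all treated patients if the 1-month contact is used, and not only those stopped. Reported event rates may be slightly higher. The rules for stopping treatment and for clinical management are not touched.

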### Case exclusion criteria

2.8

These will include cases with violation of inclusion or exclusion criteria; patients included in the wrong treatment group; and patients who withdraw from the trials, use prohibited drugs or treatments in combination, and with insufficient data.

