### Statistical analysis

2.17

A third-party medical statistics professional (Guangdong Provincial Hospital of Traditional Chinese Medicine) will perform statistical analysis. After the subject research plan and case report form are reviewed by experts, a third party will formulate a statistical analysis plan and determine the statistical software to use.

1.Full Analysis Data Set (FAS): A total of 252 random numbers were designed in this study to exclude subjects in a minimum and reasonable manner according to the principle of intentionality analysis. This data set includes all subjects receiving treatment. Missing data for key indicators are carried forward to the closest observation (LOCF).2.Per-Protocol Data Set: those who have good compliance (who have received at least 2/3 or more of the courses of treatment), whose main indicators of observation are not missing, who have basically not violated the Protocol, and who meet the inclusion criteria without any exclusion indicator constitute the current PP population. Missing data in this data set is not carried forward, but is treated as missing data.

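### Section 2.8 excludes patients after randomisation without naming an analysis set, which conflicts with the intention-to-treat full analysis set in 2.17 and the drop-out rule in 2.6

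*Protocol article*

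**What the plan says.** All places are in the protocol article.

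- **2.8 Case exclusion criteria.** The list begins "These will include cases with violation of inclusion or exclusion criteria", goes on to "patients included in the wrong treatment group; and patients who withdraw from the trials", and ends with those who "use prohibited drugs or treatments in combination, and with insufficient data". It names no analysis set. The entry exclusions stand separately in 2.5.
- **2.17 Statistical analysis.** The FAS is meant to "exclude subjects in a minimum and reasonable manner according to the principle of intentionality analysis", which I read as intention-to-treat. Membership is then fixed: "This data set includes all subjects receiving treatment". Missing key indicators are filled by last observation carried forward (LOCF). The per-protocol set has its own conditions (at least two-thirds of treatment, main indicators present, essentially no protocol violation, eligibility met) and does not refer to 2.8.
- **2.6 Drop-outs.** Voluntary withdrawal and insufficient data count as drop-out. All observation data from drop-outs are to be collected for analysis. The last sentence tells the researcher to "enroll more than one treatment course to be included in the efficient statistics". No course is defined within the two-week treatment.
- **2.7 Discontinued cases.** "The last obtained result will be used as the final result", and it enters the efficacy analysis.
- **2.16 Sample size.** The 30% allowance is introduced as covering both drop-out and elimination.

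**The concern.** Apart from eligibility violations, every item in 2.8 arises after the patient has entered the trial. Removing such patients conditions the comparison on events that the treatment can influence. Section 2.15 says blinding is difficult and offers only assessors who are not told the grouping. Patients and therapists can tell needling from exercises, so withdrawal and use of other treatments may differ by arm and may depend on how the patient is doing.

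At stake is who is in the main comparison. With two incompatible rules in one document, an analyst could follow either and cite the protocol for it. With a planned loss allowance of 30%, the choice could affect many patients.

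**Working it through.** **Step 1. Follow individual patients through the text.**

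| Patient | 2.6 | 2.7 | 2.8 | 2.17 FAS |
|---|---|---|---|---|
| Withdraws voluntarily after a few sessions | data collected; apparently counted if past one course | not addressed | excluded | kept, LOCF |
| Receives the wrong group's treatment | not addressed | not addressed | excluded | kept (was treated) |
| Uses a prohibited co-treatment | not addressed | not addressed | excluded | kept |
| Discontinued for an adverse reaction or deterioration | also a drop-out ground | last result analysed | not listed as such | kept, LOCF |
| Randomised, never treated | not addressed | not addressed | excluded if counted as withdrawn | not in FAS |

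The first three rows show the conflict between 2.8 and 2.17; the first also involves 2.6. The fourth row shows that 2.7 and 2.17 agree. The fifth shows that the FAS itself falls short of all randomised patients.

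**Step 2. Reproduce the plan's own figure.** Section 2.16 gives 80% against 93.3% and 97 per group. Alpha and power are not stated; I assume two-sided 0.05 and 80%. With the arcsine formula, h = 2·asin(√0.933) − 2·asin(√0.80) = 0.4036, and n = 2·((1.960 + 0.842)/h)² = 96.3, so 97. Then 97 × 1.3 = 126.1, the stated 126. The planned effect is 0.933 − 0.800 = 0.133.

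**Step 3. Size of the possible bias.** Let the true rate be p = 0.80 in both arms, d the share excluded from an arm, and r the response rate among those excluded. The rate among those retained is (p − d·r)/(1 − d). Neither d nor r by arm is given in the document, so all values below are assumptions.

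*One-sided illustration:* d = 0.10 and r = 0 in one arm (about 13 of 126), no exclusion in the other. The retained rate is 0.80/0.90 = 0.889. The spurious difference is 0.889 − 0.800 = 0.089, and 0.089/0.133 = 0.67 of the planned effect. A pooled two-sided 0.05 z-test with 126 randomised per arm then rejects about 47% of the time. If the same patients stay in and count as non-responders, the expected difference is 0 and the test rejects about 5%.

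*Mixed prognosis among those excluded, all within a 30% loss:*

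| Excluded (acupuncture / control) | Response among excluded | Apparent rates | Difference | Rejection |
|---|---|---|---|---|
| 30% / 30% | 50% / 50% | 92.9% / 92.9% | 0 | 5% |
| 20% / 10% | 50% / 50% | 87.5% / 83.3% | 4.2 points | 14% |
| 15% / 15% | 40% / 80% | 87.1% / 80.0% | 7.1 points | 28% |
| 30% / 10% | 50% / 50% | 92.9% / 83.3% | 9.5 points | 53% |
| 30% / 30% | 50% / 80% | 92.9% / 80.0% | 12.9 points | 71% |

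The first row matters as much as the last: heavy exclusion with equal share and equal prognosis gives no bias under the null.

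**The case against.** The best defence is that 2.8 describes per-protocol exclusions. It does not say that its cases leave the FAS, only 2.17 defines analysis sets, and the per-protocol conditions there cover much the same ground: missing main indicators, protocol violations, eligibility and, through the two-thirds rule, most withdrawals. That reading is plausible and would remove most of the conflict. It is nowhere stated, however, and the 2.16 allowance for elimination as well as drop-out fits a plan in which such cases really leave the analysis. So a reader may not infer that 2.8 certainly strips the FAS, nor that it certainly does not.

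Other limits stand:

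- A reader might infer that all four sections contradict one another. They do not: 2.7 and 2.17 agree on using the last result.
- A reader might take 2.6 to admit drop-outs only after more than one course. That sentence is garbled, does not contain the word only, and follows one that collects all drop-out data for analysis. It appears to set a condition; more cannot be said.
- The document does not say which set is primary. That may be left to the separate analysis plan and is not faulted here. It does mean that nothing shows the main analysis would follow 2.8.
- The illustration is an extreme case. With 80% responding, 10% of the arm is half of all its non-responders.
- It is tempting to scale it up to the 30% allowance. That is impossible: 0.80/0.70 = 114%. The 30% is also one allowance applied to both groups, not a difference between them.
- Limiting an FAS to treated patients is a common modification, and nothing suggests that many will go untreated.
- The arithmetic uses the effective rate from 2.16, whereas the primary outcomes in 2.10.1 are the SSA and VFSS.

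**Conclusion.** The point holds as a contradiction in the stated rules. Section 2.8 excludes patients whom the 2.17 FAS keeps and whose data 2.6 collects for analysis, and nothing limits 2.8 to the per-protocol set. The undefined course condition in 2.6 adds to the uncertainty. The treated-only FAS is a lesser departure from intention-to-treat.

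The consequence is conditional. Bias under the null requires that 2.8 be applied to the main comparison and that the share or prognosis of those excluded differ between arms. Treatment known to patients and therapists makes such a difference plausible, but the document gives no figures for it. Under the assumptions shown, the apparent effect ranges from 0 to about 13 points: 8.9 points in the one-sided illustration, against a planned 13.3. These figures show what could happen; they do not predict this trial's result.

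**What to change.** 1. In 2.8, state that the listed exclusions apply only to the per-protocol set. Say the same of the course condition in 2.6, and define a course or delete the condition.
2. In 2.17, define the FAS as all randomised patients, analysed in the group assigned by the central system, whatever treatment they received or completed.
3. Use the FAS for the main comparison, with the per-protocol set as supportive.
4. Reconcile 2.6, 2.8 and 2.17 to that definition. Section 2.7 already fits it.

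The cost is protocol wording only; no clinical procedure changes. The small downside is that a few untreated or non-compliant patients will dilute the estimate.

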### Sample size calculation

2.16

Referring to Liu Zhishun's “clinical study on acupuncture treatment of chronic moderate and severe dysphagia in stroke,” the effective rate of traditional rehabilitation is 80%, the estimated effective rate is 93.3%. According to the preset parameters, the effectiveness of the two groups were calculated with PASS 8.0 software, and 97 samples were needed for each group. At the same time, abscission and elimination were considered. The abscission rate was 30% and each group needed 126 samples. Therefore, 252 subjects were expected to be included in this study.

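### Section 2.8 excludes randomised cases without naming an analysis set; read literally, it conflicts with the full analysis set in 2.17 and with 2.6 and 2.7

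*Protocol article*

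**What the plan says.** Section 2.8 (Case exclusion criteria) is separate from the enrolment exclusions in 2.5. It begins "These will include cases with violation of inclusion or exclusion criteria", continues with "patients included in the wrong treatment group; and patients who withdraw from the trials, use prohibited drugs or treatments in combination", and ends with insufficient data. It does not say from which analysis these cases are excluded.

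Section 2.17 (Statistical analysis) defines two sets.
- The FAS is meant "to exclude subjects in a minimum and reasonable manner according to the principle of intentionality analysis". On membership it says "This data set includes all subjects receiving treatment". Missing key indicators are filled by last observation carried forward (LOCF).
- The per-protocol (PP) set needs at least two thirds of the treatment courses and no missing main indicator. It is limited to those "who have basically not violated the Protocol, and who meet the inclusion criteria without any exclusion indicator constitute the current PP population". Nothing is carried forward. Section 2.8 is not mentioned.

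Section 2.6 counts voluntary withdrawal and insufficient observation data as drop-out and says "All observation data from drop-out cases will be collected for analysis by the project teams". Its last sentence, which is hard to read, appears to admit drop-outs with more than one treatment course to the efficacy statistics. Section 2.7 carries the last result of a discontinued patient into the efficacy analysis.

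Section 2.16, when it inflates the sample size, says "At the same time, abscission and elimination were considered", so elimination is treated as a loss alongside drop-out. Section 2.15 says blinding of treatment is difficult and that assessors will not be told the group.

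**The concern.** Wrong-group treatment, withdrawal, prohibited co-treatment and insufficient data all arise after allocation. An eligibility violation that reaches 2.8 was missed at the screening that 2.14 places before randomisation. The section therefore acts on randomised patients. One analyst following 2.8 and another following 2.17 would analyse different people.

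The choice matters because treatment is open and the arms receive different active therapies. Withdrawal and extra treatment can depend both on the arm and on how the patient is doing. Removing such patients from the main comparison conditions it on behaviour after randomisation. That can produce a difference between equal treatments or hide a real one. Removing patients treated in the wrong group also gives up the randomised allocation for them.

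**Working it through.** **1. The rules side by side**

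| Case listed in 2.8 | FAS (2.17) | 2.6 | PP set (2.17) |
|---|---|---|---|
| Eligibility violation | In if treated, subject to minimal exclusion | Not addressed | Out |
| Wrong treatment group | In if treated | Not addressed | Out, as a protocol violation |
| Withdrawal | In if treated, LOCF | Drop-out; data kept for analysis | Out if under two thirds of courses or main indicator missing |
| Prohibited co-treatment | In if treated | Not addressed | Out, as a protocol violation |
| Insufficient data | In if treated, LOCF | Drop-out; data kept for analysis | Out if main indicator missing |

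The conflict is sharpest for withdrawal and insufficient data. These are the cases that LOCF exists to retain and whose data 2.6 keeps. Section 2.7 points the same way for discontinued patients, although 2.8 does not name them as such. The last column shows that the list in 2.8 largely matches the PP definition.

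**2. The plan's own figures (context only)**

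Section 2.16 gives rates of 80% and 93.3%, 97 per group before loss, a 30% abscission rate and 126 per group. Alpha and power are not stated. Assuming two-sided 0.05 and 80% power, the arcsine formula has h = 2·asin(√0.933) − 2·asin(√0.80) = 0.404 and n = 2·((1.960 + 0.842)/h)² = 96.3, so 97. Then 97 × 1.3 = 126.1, giving 126. The assumed effect is 93.3 − 80 = 13.3 points. The article gives no separate rate for elimination.

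**3. What exclusion could do if applied to the main analysis**

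Assumptions, none of them from the documents except the 80% rate and 126 per arm:
- no true effect, with 80% response in both arms;
- a share f of each arm is removed;
- the removed patients respond at rate r.

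The rate among those retained is (0.80 − f·r)/(1 − f). With r = 0.80 in control, the control rate stays at 80%. With r = 0.60 in acupuncture:
- f = 5%: (0.80 − 0.03)/0.95 = 81.1%, a difference of 1.1 points;
- f = 10%: (0.80 − 0.06)/0.90 = 82.2%, a difference of 2.2 points.

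The false-positive rate is that of a two-sided 5% pooled z test with 126·(1 − f) per arm. For f = 10%, n = 113.4, the pooled standard error is 0.0520 and the unpooled one is also 0.0520. The upper tail is at (1.96 × 0.0520 − 0.0222)/0.0520 = 1.53 and the lower at −2.39, which together give 7.1%.

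| Removed per arm | r acupuncture / control | Spurious difference | False positives |
|---|---|---|---|
| 5% | 60% / 80% | 1.1 points | 5.5% |
| 10% | 60% / 80% | 2.2 points | 7.1% |
| 5% | 40% / 80% | 2.1 points | 7.0% |
| 10% | 40% / 80% | 4.4 points | 14.1% |
| 10% | 60% / 60% | 0 | 5.0% |
| 20% (upper scenario) | 60% / 80% | 5.0 points | 15.4% |
| 30% (upper scenario) | 60% / 80% | 8.6 points | 34.5% |

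Swapping the arms reverses the sign of the difference, so the bias could also work against acupuncture.

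**The case against.** The best defence is that 2.8 is simply the PP rule without its label. Analysis sets are defined only in 2.17, and the list in 2.8 largely mirrors the PP criteria there. Allowing for PP exclusions when inflating a sample size is ordinary practice, so the mention of elimination in 2.16 does not show that anyone leaves the FAS. This stands: a reader might infer that 2.8 takes these patients out of the FAS or out of the trial, and the article never says so. It does not dispose of the point. Section 2.17 sets its own PP criteria without using 2.8, and its allowance for minimal and reasonable exclusion could be cited to bring 2.8 into the FAS.

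A second defence is that assessors are kept unaware of group (2.15), data are reviewed blind before lock (2.13) and a third party writes the analysis plan (2.17). These limit selection when cases are classified. They do not prevent withdrawal, co-treatment or wrong-group treatment from arising differently by arm during open treatment.

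Third, the size is assumed. The table's biased rows make losses outcome-related in acupuncture only, although poor progress could drive exclusions in either arm. Equal shares with equal response give no bias. A reader might also take 30% as the elimination rate and conclude that about a third of null trials would be falsely positive. Section 2.16 calls the 30% an abscission rate, and 2.6, 2.7 and the LOCF rule keep much of that loss in the analysis. The 20% and 30% rows are therefore upper scenarios only.

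**Conclusion.** The concern holds as a conflict in the current text, and it is more than missing detail. Section 2.8 states an exclusion rule for randomised patients with no analysis set attached. Followed literally, that rule gives a different efficacy population from 2.17 and runs against 2.6 and 2.7. The documents do not establish that the main analysis will be run on the reduced population, or that it would be biased if it were.

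The bias depends on exclusions that are related to outcome and differ by arm. At 5% to 10% removed per arm, with excluded patients responding at 60% under acupuncture and 80% under control, it is about 1 to 2 points against an assumed effect of 13.3, with false positives of about 5.5% to 7%. It is larger if the excluded acupuncture patients do worse, and zero if losses are equal and respond alike.

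**What to change.** - In 2.8, state that these criteria define exclusion from the PP set only, and align the list with the PP criteria in 2.17.
- In 2.17, state that FAS patients are analysed in their allocated arm, including those given the wrong treatment or a prohibited co-treatment and those who withdraw.
- Report the 2.8 exclusions, with reasons, by arm.

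This does not require redefining the FAS as all randomised patients. The article's all-treated definition can stay, and whether to widen it is a separate question.

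The cost is wording in two sections and one table in the report, with no extra patients or visits. The downside is small: patients with contaminated treatment stay in the main analysis, so the estimate may be slightly less favourable. The PP analysis remains available beside it.
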